## Abstract

**Background:**

Precision oncology, defined as treatment of patients with targeted therapies matched to specific molecular alterations, has entered routine clinical practice. Particularly in patients with advanced cancer or hematologic malignancies, for whom no further standard therapies are available, this approach is increasingly applied as last resort option outside of the approved indication. However, data on patient outcomes are not systematically collected, analyzed, reported, and shared. We have initiated the INFINITY registry to provide evidence from routine clinical practice to fill this knowledge gap.

**Methods:**

INFINITY is a retrospective, non-interventional cohort study conducted at approximately 100 sites in Germany (office-based oncologists/hematologists and hospitals). We aim to include 500 patients with advanced solid tumors or hematologic malignancies who received a non-standard targeted therapy based on potentially actionable molecular alterations or biomarkers. INFINITY aims to provide insights into the use of precision oncology in routine clinical practice within Germany. We systematically collect details on patient and disease characteristics, molecular testing, clinical decision-making, treatment, and outcome.

**Discussion:**

INFINITY will provide evidence on the current biomarker landscape driving treatment decisions in routine clinical care. It will also provide insights on effectiveness of precision oncology approaches in general, and of specific drug class/alteration matches used outside their approved indications.

**Trial registration:**

The study is registered at ClinicalTrials.gov, NCT04389541.

## Background

Oncology is currently experiencing a paradigm shift from a “one-drug-fits-all” treatment model towards a tailored, molecular targeted or biomarker-driven treatment approach [1–4]. The goal is to choose the most effective, best tolerated drug for the patient, based on the molecular profile of the individual disease.

To investigate the efficacy of this novel treatment approach, new clinical trial concepts have evolved, shifting from a tumor type focus to a molecular profile focus. Thus, biomarker-guided trial designs have recently emerged, such as basket trials allocating patients to matched treatments based on molecular alteration across cancer types, or umbrella trials involving one cancer type and different treatments matched to genomic alterations [2, 5].

Several precision oncology trials have shown promising results, suggesting that molecular-matched targeted therapy has the potential to improve outcomes compared to conventional therapy [2, 6–11]. However, it is difficult to conduct biomarker-driven clinical trials and thus, reliable evidence from randomized trials is still lacking. In this context, real-world data are a valuable data source with the potential to address and couple real-world molecular and clinical data and to provide deep insights also into sequential treatment decisions and overall outcomes.

The number of available targeted drugs is steadily increasing [12, 13]. First drugs have been approved in a tumor-agnostic manner based on the presence of molecular alterations instead of specific tumor types: In 2017, the Food and Drug Administration (FDA) granted the first tumor-agnostic approval for pembrolizumab for patients with unresectable or metastatic, microsatellite instability-high or mismatch repair deficient (MSI-H/dMMR) solid tumors. As of 2021, four tumor-agnostic FDA approvals have been granted for three drugs (pembrolizumab, larotrectinib and entrectinib) based on three molecular alterations (MSI-H/dMMR, *neurotrophic tyrosine receptor kinase* (*NTRK*) gene fusion and high tumor mutational burden (TMB-H)) [14]. Furthermore, a growing number of targeted therapies has been approved in more than one tumor type based on specific molecular alterations (e.g., BRAF, HER2/ERBB2, RET, BRCA1/2, PD-L1) including the approval of dabrafenib/trametinib for pediatric patients with BRAF V600E mutant glioma and selpercatinib, a selective kinase inhibitor for patients with rearranged during transfection (RET) fusion-positive tumor by 2023 [5, 15, 16].

Besides conventional diagnostic techniques including polymerase chain reaction (PCR), immunohistochemistry (IHC), (fluorescent) in situ hybridization ((F)ISH), reverse transcription PCR (RT-PCR) and microarrays, next generation sequencing (NGS) techniques have transformed the diagnostic field and are now broadly available [5, 11].

Increasing availability and use of NGS testing as well as targeted therapies nourish the hope that these new technologies will quickly translate into patient clinical benefits, especially in situations where no further standard treatment is available. However, clinical outcomes of this approach are not systematically collected, analyzed, and reported.

The currently available evidence on the benefit of molecular-matched therapies used outside of their approved indication still carries substantial uncertainties. The only randomized trial in the field (SHIVA) found no clear benefit for patients receiving molecular-matched treatments used outside their labeled indications compared to standard of care (PFS 2.3 vs. 2.0 months) [17]. However, this trial was conducted several years ago, and diagnostic techniques and availability of targeted therapies have improved since then. MyPathway, a multicenter, multiple basket phase IIa study, evaluates efficacy of treatments targeting molecular alterations of HER2, epidermal growth factor receptor (EGFR), BRAF and the Hedgehog pathway in subprotocols [18]. The TAPUR phase II multi-basket trial, investigating safety and efficacy of commercially available targeted antineoplastic drugs in patients with metastatic solid tumors harboring potentially actionable molecular alterations, was initiated in 2016 [19]. While proof for a clinical benefit is missing in some patient cohorts, encouraging results in other cohorts [20] provide evidence of the feasibility and potential value of the basket study design in precision medicine [18, 21, 22]. The TAPUR trial is still ongoing, but first study results already helped to further shape the field: Treatment of metastatic colorectal cancer patients with *FMS-like tyrosine kinase-3 (FLT-3)* amplification with sunitinib was found to be ineffective; while on the other hand pembrolizumab monotherapy was reported to have anti-tumor activity in metastatic breast cancer patients with TMB-H, supporting the recent FDA approval [21, 22].

The INFINITY registry will provide systematically collected real-world data on the use of molecular-matched targeted therapies outside of their approved indication for treatment of patients with advanced solid tumors or hematologic malignancies, for whom no standard therapy is available. INFINITY explores how precision oncology is applied in routine clinical practice in Germany, how decisions are made by the treating physicians, which diagnostic tests are utilized to identify potentially actionable alterations, which substance classes of targeted therapies are used, and which molecular alterations are targeted. Effectiveness of matched therapies in the total patient cohort and in patient subgroups will be analyzed, aiming to generate hypotheses on effective or ineffective drug class/alteration matches. Furthermore, a decentral tissue sample biobank is set up, collecting sample information for genomic analysis for future translational research projects.

## Methods/design

### Objectives

INFINITY collects real-world data on precision oncology in Germany with the objective to assess treatment and outcomes of adult patients with advanced solid tumors or hematologic malignancies who received a non-standard targeted therapy (NSTT; i.e., a targeted therapy used outside the labeled indication and not recommended in guidelines) based on an actionable molecular alteration or associated with biomarker(s). NSTT administered in this study will be matched to targetable genomic or proteomic alterations or matched to biomarkers (i.e. biomarker-driven precision immunotherapy / checkpoint inhibitor / targeted therapy based on biomarker(s) associated with treatment benefit also including (but not restricted to) upstream and/or downstream intracellular targets). In particular, data on patient and disease characteristics, molecular testing, physician´s decision making, treatment (assessed as substance class), and outcome will be evaluated.

### Study design

INFINITY is a retrospective, multicenter, non-interventional study, conducted at approximately 100 study sites in Germany, including hospitals and office-based oncologists. 500 patients will be enrolled over a recruitment period of 3 years, which started in April 2020.

### Eligibility criteria

Inclusion criteria:Patients with advanced solid tumors (i.e., locally advanced, inoperable and/or metastatic) or hematologic malignancies not eligible for standard therapy options (i.e., without further treatment options with drugs approved for the specific indication based on the judgement of the treating physician)Started or completed a non-standard targeted therapy based on a potentially actionable alteration or biomarker identified by molecular diagnosticsAvailability of molecular diagnostic test results that informed clinical decision to apply the non-standard targeted therapyTargeted therapy must be non-standard at time point of patient enrollment/registrationAge ≥ 18 yearsSigned and dated informed consent form (only if patient is alive at time of data entry into the project, not applicable for inclusion of deceased patients’ data)

Exclusion criteria:The non-standard targeted therapy was administered within a clinical trialThe targeted therapy is non-standard because it was given in another therapy line, without a designated prior therapy or in combination with a different chemotherapy backbone, as specified by summary of product characteristics and/or treatment guidelines.

### Data collection

Study sites are asked to retrospectively document all patients who meet the eligibility criteria (including deceased patients) until 2023.

Clinical routine data documented by study sites is structured and transferred by the site staff into a secure web-based eCRF system (iostudy office). The iostudy office edc system is a fully validated secure software that conforms to 21 CRF Part 11 requirements. As source of documentation, routine medical records are used. Sites will document data regarding patient and disease characteristics (e.g. sex, entity, staging, histology) as well as treatment details of NSTT and prior and subsequent therapies applied. The investigator’s treatment decision process is evaluated using a paper-based questionnaire comprising questions on factors influencing treatment decisions as well as information on respective potentially actionable alteration including ESCAT levels, which are transferred into the eCRF. eCRF documentation will be checked for plausibility and completeness both centrally and on-site by data managers, medical managers, and clinical monitors, respectively.

Study sites send pseudonymized diagnostic reports (e.g. pathology reports, reports on sequencing results such as NGS) and molecular tumor board (MTB) reports, if applicable, including treatment recommendations to iOMEDICO. Dedicated and trained iOMEDICO staff extracts information from the reports and enters data on all reported immunohistochemistry or mutational profiling as well as molecular alterations including complex sequencing results (including test panels and further information) into a pre-specified electronic database. These data are documented as described in the report but in analogy with the HGVS (Human genome variation society) code for proteomic und genomic sequence variants [23]. Independent checks for consistency of data entries by a second reviewer are performed. This is to ensure central quality control for these comprehensive and complex data. This structured data capture enables standardized and structured analyses.

Additionally, we have established a decentral tissue sample biobank where information on tumor samples including contact details of local pathology departments is captured. This enables us to request samples for upcoming translational research projects.

### Descriptive analyses

Regarding patient and disease characteristics as well as therapies applied, the following data will be analyzed:Patient and disease characteristics including e.g., sex, body mass index (BMI), Eastern Cooperative Oncology Group (ECOG) performance status, type of health insurance, comorbidities and tumors types, time from primary diagnosis to start of first NSTT, age at start of first NSTTDetails on NSTT including substance classes, treatment duration as well as prior and subsequent antineoplastic therapy lines

Characteristics regarding diagnostics and identified molecular alterations include the following:Frequencies: type of molecular diagnostic testing performed, proteins and genes tested, multigene panels or NGS in molecular diagnostics, type (by panel size) of NGS library sequenced, altered proteins and genes, if tested, treatment recommendations given in molecular diagnostic reports, implemented treatment recommendations given in molecular diagnostic reports, use of a MTB, implementation of the treatment recommendation given by MTBClinical decision making: Frequency of answers rated with a Likert scale on patient’s non-suitability for standard therapy options / choice of performed molecular diagnostics / choice of selected molecular target and targeted non-standard therapy / reasons for the selection of targeted non-standard therapy / primary goal of the non-standard targeted therapy / expected advantages of the non-standard targeted therapy and frequency of ESMO Scale of Clinical Actionability for molecular Targets (ESCAT) evidence levelsTurnaround times:◦ Duration from sample receipt to molecular testing result◦ Duration from molecular testing result to start of NSTT

### Effectiveness outcomes

Effectiveness of non-standard targeted therapy will be analyzed as follows:Overall survival (OS)Progression-free survival (PFS)PFS ratio (i.e., PFS of non-standard targeted therapy divided by PFS of preceding therapy)Time to treatment failure (TTF)TTF ratio (i.e., TTF of non-standard targeted therapy divided by TTF of preceding therapy)Tumor response: Best overall response (BOR); overall response rate (ORR); disease control rate (DCR); Time to Response (TTR); Duration of Response (DOR)

### Statistical analysis

No formal sample size calculation was performed. The sample size of 500 patients has been chosen to enable subgroup analyses for e.g., specific tumor entities with a predefined minimum number of patients. For example, given the distribution of patients for specific tumor entities from the MOSCATO trial [8], we expect 50 patients or more in each of the following cancer entities: head and neck cancer, gastrointestinal cancer, lung cancer, breast cancer und genitourinary cancer. Furthermore, given 100 recruiting sites with 1-2 eligible patients per year and 4 documentation periods, it can reasonably be expected to reach the sample size of 500 patients in time.

All patients fulfilling the eligibility criteria and with documented start date of NSTT will be included in the full analysis set (FAS). All variables will be analyzed in a descriptive manner. Categorical variables will be presented as absolute and relative frequencies and continuous variables as number of observations, median and range. Time-to-event variables (PFS and OS) will be analyzed using the Kaplan-Meier method. PFS is defined as the time from start of therapy to date of documented tumor relapse/progression or death due to any cause, whichever comes first. OS is defined as the time from start of therapy to date of death due to any cause. Patients with no event will be censored at the date of last contact or start of subsequent systemic therapy. The PFS ratio will be calculated to compare PFS of NSTT with time to progression (TTP) of preceding antineoplastic therapy for each patient. BOR is defined as best documented response achieved under NSTT. DCR is defined as proportion of patients who achieved complete response (CR), partial response (PR) or stable disease (SD) as best response; ORR is defined as proportion of patients who achieved either CR or PR as best response. TTR is defined as time from start of treatment to first objective response observed for patients who achieved a CR or PR. DOR is defined as time from documentation of tumor response to disease progression or death from any cause. TTF is defined as time from start of therapy to discontinuation of treatment for any reason, including progression, toxicity, and death.

Patient subgroups based on different substance classes will be analyzed separately. Provided that numbers are sufficient, further subgroups will be analyzed, e.g. by tumor entity, biomarker, intervention. All subgroup analyses will be considered exploratory.

Interim analyses are planned to be conducted after each data collection phase (2020, 2021, 2022) and a final analysis will be conducted at the end of study (2023).

Statistical analyses will be performed using SAS software, version 9.4 or higher and R version 4.0.3 or higher.

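### PFS shares one censoring rule with OS, so time after the last tumour assessment counts as progression-free; the PFS curve can only be equal or higher, by an unknown amount

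*Protocol article*

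**What the plan says.** All the relevant rules are in the article's Statistical analysis section.

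- Estimator: "Time-to-event variables (PFS and OS) will be analyzed using the Kaplan-Meier method".
- PFS event: "date of documented tumor relapse/progression or death due to any cause, whichever comes first", counted from the start of therapy.
- OS: "OS is defined as the time from start of therapy to date of death due to any cause".
- Censoring, in one sentence after both definitions and with no distinction between them: "Patients with no event will be censored at the date of last contact or start of subsequent systemic therapy". The part chiefly at issue for PFS is its opening: "Patients with no event will be censored at the date of last contact".

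The same section uses PFS on the non-standard targeted therapy (NSTT) as the numerator of the PFS ratio.

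Under Study design, the article states that "INFINITY is a retrospective, multicenter, non-interventional study". Data collection names routine medical records as the source. The article describes no schedule of tumour assessment.

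**The concern.** The two endpoints need different information at the censoring date. At last contact it is known whether the patient is alive, so that date suits OS. Whether the tumour has progressed is known only as of the last time someone assessed it. If a patient stops being assessed but remains in contact and starts no further systemic treatment, the rule keeps that patient in the PFS risk set as progression-free until last contact. If a further treatment does start, the excess ends there, but that date normally also falls after the last assessment.

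PFS is one of the listed effectiveness outcomes and feeds the PFS ratio. The registry intends to use effectiveness data to generate hypotheses about which drug class and alteration matches work. A rule that can move PFS in one direction only, upwards, matters for that use even though the analysis is descriptive, because the estimate itself is shifted.

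**Working it through.** The article prints no figure that depends on the censoring rule, so there is nothing to reproduce. The direction follows from the text. The size needs assumptions.

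**1. Direction.** The Kaplan-Meier estimate is S(t) = product over event times of (1 − d/n), with d events and n patients at risk. Take the same events under both rules. For each patient without an event, last contact (or next-treatment start) is no earlier than the last assessment before it. So n under the written rule is at least as large at every event time, each factor is at least as large, and the curve is never lower. It is identical where no event falls inside anyone's gap. In the PFS ratio, the numerator of a patient without an event is likewise equal or longer.

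**2. Closed form, assuming exponential PFS.** Median = ln 2 × person-time / events. Let c be the share without an event, g the mean gap from last assessment to the written censoring date, and m the mean time per patient to event or last assessment. The written rule multiplies the median by (m + c·g)/m = 1 + c·g/m. With m assumed to be 6 months:

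- c = 10%, g = 1 month: 1 + 0.1/6 = 1.017
- c = 20%, g = 3 months: 1 + 0.6/6 = 1.10 (median 5.20 becomes 5.72 months)
- c = 30%, g = 3 months: 1 + 0.9/6 = 1.15
- c = 40%, g = 6 months: 1 + 2.4/6 = 1.40

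The documents give none of c, g or m.

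**3. Simulation without the next-treatment limit.** Assumptions: 400,000 patients per scenario, exponential progression, median survival after progression 5 months, data cut uniform over 1 to 24 months, and 15% or 30% leaving assessment (mean 3 months) while staying in contact. Entries are median PFS in months and, in brackets, 6-month PFS.

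| True median; share leaving | Truth | Written rule | Last assessment | Written minus last assessment |
|---|---|---|---|---|
| 3.5; 15% | 3.5 (30.6%) | 3.8 (34.2%) | 3.6 (32.0%) | 0.2 (2.2 points) |
| 3.5; 30% | 3.5 (30.4%) | 4.1 (37.5%) | 3.7 (33.3%) | 0.4 (4.2 points) |
| 2.3; 15% | 2.3 (16.4%) | 2.4 (20.2%) | 2.4 (18.2%) | 0.0 (2.0 points) |
| 2.3; 30% | 2.3 (16.3%) | 2.6 (23.9%) | 2.5 (20.2%) | 0.1 (3.7 points) |

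The value 2.3 months is the matched-therapy PFS that the Background quotes from the randomized trial. It serves only as one end of the assumed range.

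**4. Simulation with the next-treatment limit.** Assumptions: 400,000 patients, a scan every 2 months, median survival after progression 6 months, last contact uniform over 3 to 24 months, and 40% of patients with unseen progression starting a next treatment and being censored there. Six-month PFS with 20% stopping imaging:

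| True median | Truth | Written rule | Last assessment | Written minus last assessment |
|---|---|---|---|---|
| 2.3 | 16.3% | 22.4% | 18.3% | 4.1 points |
| 4 | 35.3% | 39.3% | 36.2% | 3.1 points |
| 6 | 50.1% | 52.5% | 50.4% | 2.1 points |

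With 10 to 50% stopping imaging the difference runs from about 1 to 10 points. With nobody stopping, 6-month PFS is practically the same under both rules. Medians from this model are not used for sizing: progression is detected only on the 2-month scan grid, so medians jump between scan dates.

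**The case against.** Several points against the concern stand, and they limit it.

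- **The rule does not credit all later time.** Quoted only as far as last contact, the sentence seems to run on indefinitely. The next-treatment clause stops the clock for everyone who moves to another line, and subsequent lines are collected. It limits the excess but does not remove it.
- **The gap to the truth is not the effect of the rule.** In the first simulation a true median of 3.5 months becomes 3.8 to 4.1, and a reader might infer that the censoring rule costs 0.3 to 0.6 months. Last-assessment censoring itself gives 3.6 to 3.7. The rest comes from late deaths after undocumented progression. The rule accounts for 0 to 0.4 months.
- **The premises about follow-up are assumed.** Last contact is not defined, so it may or may not be a visit with an assessment. The eligibility wording, "without further treatment options with drugs approved for the specific indication based on the judgement of the treating physician", concerns treatment options and says nothing about imaging. Documented progression may be clinical, deaths still count as events, and few patients in this population may be alive without an event.
- **Subgroup distortion is not shown.** If assessment intensity differs between entities or sites, the excess would differ too, but this was not calculated. Nor does the article rank PFS as a main outcome; it lists it with others and calls subgroup analyses exploratory.
- **Sampling error in a subgroup is larger.** Assume exponential PFS, a median of 3.5 months and events in 80%. A 50-patient entity then has 40 events and a 95% half-width of about 1.96 × 3.5/√40 = 1.1 months. This is a fair comparison for subgroups, but the shift does not shrink with numbers. For all 500 patients (400 events) the half-width is 1.96 × 3.5/√400 = 0.34 months, about the upper end of the shift.

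That details may lie in an unseen analysis plan is no answer here, because the article states the rule.

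**Conclusion.** The concern holds in limited form. One sentence censors both endpoints on dates that suit vital status, and for PFS it counts unassessed time as progression-free. The direction is certain: PFS equal to or higher than under last-assessment censoring, and likewise the PFS-ratio numerator in patients without an event.

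The size is unknown, because the article gives neither the share of patients no longer assessed nor the gap to last contact. On the assumptions shown, the rule adds about 0 to 0.4 months to the median (15 to 30% leaving assessment, next-treatment limit not modelled) or about 2 to 4 percentage points to 6-month PFS (20%, limit modelled). The effect on 6-month PFS is near zero if assessment continues to last contact. The documents do not support saying that PFS will be materially overstated in this registry. They support saying that the stated rule allows it and that a small change would settle the question.

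**What to change.** Split the censoring sentence by endpoint.

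- **PFS:** censor patients without an event at the last documented assessment, imaging or clinical, that shows no progression and falls on or before the start of any further systemic treatment. If there is none, censor at NSTT start. The limit at further treatment must stay. Without it, a stable scan on the next line would credit that line's time to NSTT.
- **OS:** censor at last contact. Read literally, the present sentence also censors OS at the next systemic treatment, so the OS rule needs its own wording.
- **Sensitivity:** report PFS under the written rule beside the new one. If the two agree, robustness is shown; if they differ, readers can see by how much.

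Cost: a sentence or two in the analysis section, slightly shorter PFS follow-up, and one extra date. The Data collection section does not name the last progression-free assessment as a collected item. Sites would have to supply it from routine records, which may mean queries to some of the roughly 100 sites. Last-assessment censoring does not remove all the error, since deaths after unseen progression still enter as late events.

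### One censoring rule serves both PFS and OS, so OS is cut at the start of the next systemic therapy and the curve no longer estimates time to death from any cause

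*Protocol article*

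**What the plan says.** All the relevant text is in the protocol article.

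- **Endpoints and method** (Statistical analysis): "Time-to-event variables (PFS and OS) will be analyzed using the Kaplan-Meier method".
- **PFS** runs from treatment start until a recorded progression or until the patient dies, taking the earlier of the two.
- **OS**: "OS is defined as the time from start of therapy to date of death due to any cause".
- **Censoring**, in the sentence directly after the OS definition: "Patients with no event will be censored at the date of last contact or start of subsequent systemic therapy".

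The article gives no other censoring rule. Nothing limits this one to PFS, and no wording assigns one date to each endpoint.

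Under Data collection, sites record "treatment details of NSTT and prior and subsequent therapies applied", so later lines are expected and dated. The same section says: "Study sites are asked to retrospectively document all patients who meet the eligibility criteria (including deceased patients) until 2023". Deaths after a later line can therefore be known.

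**The concern.** For PFS, censoring at a new therapy is a recognised option. For OS as defined here it is not, because a patient who moves to another therapy remains at risk of death and remains observable. The rule can be read in two ways, and both damage the OS curve.

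- **Literal reading** (only patients without an event are cut). A patient who switches and dies is followed to death. A patient who switches and is still alive is cut back to the switch date. Whether follow-up after the switch counts then depends on how it ended. Survivors lose time at risk, decedents do not, and the estimate is pushed down.
- **Broad reading** (everyone is cut at the switch). All later deaths are discarded. Patients leave the risk set because they have progressed and are fit for more treatment, so those who remain do not represent them. The bias can go either way.

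Both readings break the independent-censoring assumption of the Kaplan-Meier method. The distortion also depends on the share of patients who get a further line. OS is listed first among the effectiveness outcomes, results are to be analysed by substance class and, numbers permitting, by entity and biomarker, and the Background section aims at hypotheses about effective and ineffective matches. Where switching differs between subgroups, the rule alone can create OS differences.

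**Working it through.** The article states no OS figure, so there is nothing to reproduce. The defect follows from setting the OS definition beside the censoring sentence. The simulation below only illustrates its size.

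**Input from the document.** Median PFS of 2.3 months, the matched arm of the randomized trial cited in the Background ("PFS 2.3 vs. 2.0 months"), used as the median time to progression.

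**Assumed inputs (not in the document).**
- Exponential times, with a median time to progression of 4.0 months as an alternative.
- 30%, 50% or 70% of patients eligible for a next therapy, starting on average 0.7 months after progression.
- Median survival after progression of 8 months with a next therapy, and 8, 4 or 2 months without.
- Administrative censoring uniform over 3 to 36 months.

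This gives 2 × 3 × 3 = 18 scenarios, each with 400,000 patients.

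**Analyses compared.** Let T be the death time, C the last contact and S the start of next therapy (infinite if none).
- Reference: time min(T, C), event if T ≤ C.
- Broad: time min(T, C, S), event if T ≤ C and T < S.
- Literal: if T ≤ C, time T with an event; otherwise time min(C, S), censored.

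**Results for time to progression 2.3 months and 50% eligible:**

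| Post-progression median without next therapy | Reference: median OS; 12-month OS | Literal | Broad | Deaths discarded (broad) |
|---|---|---|---|---|
| 8 months | 11.6; 48% | 10.5; 43% | 12.8; 53% | 46% |
| 4 months | 9.2; 37% | 8.4; 30% | 9.0; 34% | 41% |
| 2 months | 7.5; 29% | 6.8; 22% | 6.9; 20% | 39% |

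Medians are in months. At 24 months the literal reading gives 11%, 4% and 2%, against 17%, 11% and 9% in the reference.

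**Range over all 18 scenarios.**
- Literal: the median falls in every scenario, by 0.3 (6.4 to 6.1) to 1.6 months (14.2 to 12.6). 12-month OS falls by about 2 to 10 points.
- Broad: the median moves by −0.6 (7.5 to 6.9) to +4.4 months (14.2 to 18.6), and 12-month OS by about −9 to +13 points. Between 22% and 64% of observed deaths are discarded.

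**Effect on subgroup comparisons.** Take two subgroups with identical true survival: time to progression 2.3 months, post-progression median 8 months for everyone, true 12-month OS 48%. One has 30% eligible for a next line and the other 70%. The broad reading reports 51% and 58%, a spurious gap of 58 − 51 = 7 points. The literal reading reports 45% and 41%, a spurious gap of 45 − 41 = 4 points in the opposite direction.

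**A separate set of assumptions gives the same pattern.** With a median time to progression of 4 months, 50% switching at progression, and post-progression medians of 8 months with and 3 months without a further line, the literal reading takes 12-month OS from about 45% to 39%. The broad reading takes the share of patients with an OS event from 69% to 39%.

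**The case against.** The strongest reply is that the sentence is compressed and was meant distributively: last contact for OS, subsequent therapy for PFS. That would fit the OS definition, and the full protocol or SAP, which is not shown, may say so. The intention is plausible. However, the text has no word that distributes the dates. Matched in the order written (PFS then OS; last contact then subsequent therapy), it would give subsequent therapy to OS. This is also not a complaint about detail left to another document: a rule is stated, and an analyst who follows it gets the wrong OS.

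Second, the sizes rest on assumptions, and sampling error may be larger. In a subgroup of 50, the size the article names, a 12-month OS of 45% has a 95% interval of ±1.96 × √(0.45 × 0.55 / 50) = ±14 points. With all 500 patients it is ±4.4 points. This stands as a caution on small subgroups. But bias does not shrink with sample size, and in the full cohort it is comparable to the sampling error or larger.

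Third, the study is descriptive, names no primary endpoint, treats subgroups as exploratory, and already disclaims causal conclusions on subgroup differences. All true, and this limits the consequences. A descriptive curve must still estimate the quantity it is labelled with.

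Fourth, counting a death after an unrecorded progression as a PFS event is an accepted convention. That is fair, and the PFS point is secondary. What is not acceptable is one convention for patients who die and another for those who survive, which the literal wording produces.

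**Conclusion.** The concern holds. As written, start of subsequent systemic therapy is a censoring date for OS. This conflicts with the article's own definition of OS and makes censoring informative on either reading. That conclusion needs no simulation.

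Under the literal reading the bias is downward: 0.3 to 1.6 months in the median over the scenarios examined. Under the broad reading the direction is not fixed, and roughly a fifth to two thirds of observed deaths are lost. These sizes depend on assumed switching shares, post-progression survival and follow-up, and are illustrative only. If the full protocol or SAP already separates the endpoints, the analysis is safe and only the article's sentence needs correcting.

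**What to change.** Replace the single sentence with one rule per endpoint.

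- **OS:** patients not known to have died are censored at the date last known alive, regardless of any subsequent therapy.
- **PFS:** if censoring at subsequent systemic therapy is kept, apply it to every patient who starts such therapy before a documented progression, including those who die later. Patients with neither an event nor a new therapy are censored at last contact.

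The cost is one sentence in the protocol or SAP and a change to the derivation program. Death and last-contact dates are already needed for OS, and subsequent therapies are already documented, so no new data are required. Any interim OS results produced under the shared rule should be rerun.
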